## Abstract

Child behavioural and mental health problems have become a public health crisis. The consequences of poor mental health in childhood have large economic costs and consequences for the individual, their families, and for society. Early intervention through parenting programmes can reduce the onset of poor mental health in childhood, hence evaluating the effectiveness of parenting programmes is critical. The ‘Incredible Years Toddler’ parent programme is an education and training intervention designed to enhance the social and emotional wellbeing of children aged 1–3 years. Whilst previous studies show Incredible Years Toddler to provide promising effects on child outcomes in the short term, the research samples have lacked ethnic diversity and representation from socioeconomically deprived families. This quasi-experimental study is registered on ISRCTN (ISRCTN49991769). We will investigate the effectiveness of Incredible Years Toddler being delivered in three neighbourhoods in inner city Bradford, England. These neighbourhoods contain a socially and ethnically diverse population with 84% living in the poorest decile for England and Wales. Parents with a child aged 1–3 years old who are enrolled in Born in Bradford’s Better Start interventional family cohort study are eligible for this study. Intervention participants will be matched to a demographically comparable control group using propensity score matching. This study will use retrospective and prospective data from participants who attended Incredible Years groups between September 2018 and April 2024. The required minimum sample is *n* = 1336 (ratio 1:3) to detect a small effect (odds = 1.5, *d* = .20) on the Early Years Foundation Stage profile total score at age 5; a measure of early child development that is routinely collected by teachers. We will also establish whether these effects are moderated by child age at entry to intervention, programme delivery mode, socioeconomic status, and ethnicity. We will also estimate the cost of the intervention and conduct a cost-consequence analysis.

## Introduction

Child behavioural and mental health problems have become a public health crisis. One in eight children (aged 2–19 years) in England are estimated to experience a mental health disorder [1]. The prevalence of this increased with the COVID-19 pandemic, with the incidence rising from 11% in 2017, to 16% in July 2020 for children aged 5–16 years [2] In 2022, 18% of children aged 7 to 16 years were estimated to have a probable mental disorder [3]. Further, mental health problems are exacerbated for children living in socioeconomically disadvantaged circumstances [4, 5].

When children with mental health issues reach adulthood, they are more likely to be unemployed and to have contact with the criminal justice service [6]. Poor child mental health has large economic costs and consequences for both the individual and for society, for example, the average annual costs to mental health services for 12–15-year-olds with conduct disorders are £1,789, and £1,353 for those with emotional disorders [6].

The first three years of a child’s life are a crucial time for their development, with disruptions in early neurodevelopment being a significant risk for development of later mental health problems [7, 8]. Early intervention through parenting programmes has the potential to prevent or reduce the personal and societal costs of poor child mental health [9], since some child behavioural and mental health issues may be attributable to insecure attachments and low parental sensitivity [10, 11]. Whilst group parenting programmes have been found to be effective for reducing child conduct problems and improving child socio-emotional wellbeing for parents of children aged three years or older [12, 13], evidence remains weak for the short and long-term effectiveness of parenting programmes for parents of children in the critical first three years of life, as well as in specific subgroups of parents [9, 12, 14].

### The incredible years toddler programme

One such series of programmes that may address this paucity of evidence are The Incredible Years (IY) parent programmes (www.incredibleyears.com), which are parent education and training group-based interventions informed by social learning theory and designed to enhance the social and emotional wellbeing of children aged 0–12 years. These manualised programmes are typically delivered by trained facilitators to groups of 10–12 parents for two hours a week for 12–20 weeks. This protocol outlines our plans to evaluate the Incredible Years Toddler (IY-T) programme for parents of 1-3-year-olds. In IY-T, parents learn effective strategies to help the child learn how to better manage their emotions and behaviour [15]. Whilst IY parent programmes for older children have evidence of positive short-term outcomes [14, 16], the more recently developed IY-T has less evidence in comparison.

There are only two previous studies which have investigated the effectiveness of IY-T [17, 18]. Perrin et al. [2014] conducted an RCT with 89 parents in the USA, and delivered IY Toddler through primary care (paediatric practices), rather than community settings. Significant improvements were found in parenting practices and child disruptive behaviours. Hutchings et al. [2017] conducted a community based RCT with 153 parents in Wales, and relied on geographical targeting to disadvantaged ‘Flying Start’ areas to deliver IY Toddler. Significant improvements were found in child development, home environment, and parental depression. In addition, a recent RCT of the ‘E-SEE Steps’ model (a proportionate universal approach delivering various intensities of the IY Baby and IY-T) found no significant differences in parent and child outcomes 18 months after randomisation [19]. However, the E-SEE trial was not designed or powered to establish the effectiveness of IY-T as a standalone programme.

It is of interest to know which sociodemographic groups of parents may benefit most from parenting programmes. Ethnic minorities represented 29% of the study population of the trial based in the USA [18] and no information regarding ethnicity was reported for the study based in Wales [17]. With regards to socioeconomic status, parents in the study based in Wales were living in a disadvantaged area, however, the recruited participants were less disadvantaged than parents in a comparable trial (Welsh Sure Start trial), where community disadvantage rates were lower [17, 20]. Parents in the study based in the USA had household incomes ranging between $20,000 and $100,000 [18]. The IY-T intervention therefore has limited evidence of effect in the most vulnerable populations such as those from an ethnic minority or living in areas of socioeconomic deprivation. A meta-analysis of IY parent programmes indicated that the intervention effects are not moderated by socioeconomic or ethnic groups for child conduct problems, suggesting that the programme is similarly effective for families from different backgrounds [21]. However, this meta-analysis only compared ‘White’ groups to all other ethnic minorities. This means we cannot be certain of the meaning of this finding for different ethnic minority groups, since there may be much heterogeneity regarding the programme effectiveness across different ethnic minority groups. It would, therefore, be beneficial to test whether the finding that IY parent programmes are consistently effective across different ethnic groups generalises specifically to IY-T, and generalises to other long-term outcomes.

Due to the high cost of collecting long-term data, effectiveness trials are not usually funded to explore long-term outcomes over 12 months after the intervention took place. The aforementioned evaluations of IY-T examined parent and child outcomes up to 12 months after baseline [17, 20]—which is relatively long-term compared to other effectiveness trials, however, more long-term outcome studies are needed to explore ongoing effectiveness as well as economic and societal impacts. There is some evidence that children whose parents received the IY ‘parent training and child treatment’ programme maintain positive behavioural improvements for oppositional defiant disorder and conduct disorder several years post-follow-up [22], however, studies are needed to confirm the long-term results of all IY interventions for various ages, diagnoses, and demographic populations [14].

### Methods for evaluating child and family preventative services in practice

Whilst RCTs are the most rigorous method of establishing the effectiveness of an intervention [23], they are susceptible to several issues [24, 25]. RCTs can suffer from a lack of generalisability, as participants that volunteer to participate might not be representative of the population being studied. Parents who are at the point of ‘readiness to change’ are unlikely to agree to take part in a study in which they might be randomised not to get help, resulting in recruitment bias [23, 25]. A further problem is that it is usually not possible to control the opportunities through which a parent can access an intervention; since they can be made available through third sector organisations, the internet or through books. A parent who has heard about a programme during their recruitment to a study may decide to enrol in the programme through another route (even if they are in the control group of the RCT) [25]. Finally, RCTs are susceptible to a high number of participants being lost to follow up [23], especially when a study aims to explore long term effects of the intervention.

A quasi-experimental study cannot provide the level of certainty in establishing causal effectiveness that an RCT does, as it lacks random assignment to treatment group [24, 26]. However, it has advantages in terms of efficiency and pragmatism, and can overcome the RCT design limitations outlined above, such as providing ecological validity by evaluating an intervention when delivered in its natural (non-trial) context [24]. This quasi-experimental study evaluates IY-T as delivered in the Better Start Bradford programme by Barnardo’s. Parents at the point of ‘readiness to change’ are free to enrol on this intervention immediately (or not), thus reducing recruitment bias. The participants are enrolled in the Born in Bradford’s Better Start (BiBBS) interventional family cohort study, which runs in parallel to Better Start Bradford [27]. By utilising the BiBBS cohort, this study has linkage to a routinely collected and long-term outcome, and this mitigates the risk of losing participants to follow up. Finally, the BiBBS cohort contains an ethnically diverse population (61% Pakistani heritage; 12% White British; 8% other South Asian and 6% Central and Eastern European ethnicity), with the majority (84%) living in the lowest decile of the Index of Multiple Deprivation [28]. This study therefore provides a unique opportunity to advance our understanding of the effectiveness of IY-T in an ethnically diverse and socioeconomically deprived population.

### Rationale and objectives for this study

The long-term effectiveness of IY-T has not yet been investigated using a predominantly disadvantaged and ethnically diverse cohort sample with routinely linked data. This study protocol outlines our plans to be the first to provide insights into the longitudinal effectiveness of IY-T on children’s social-emotional development and early years school skills at 5 years, approximately 2–4 years after their parents’ attendance at IY-T groups. The study objectives are to:

Establish if IY-T is effective in improving child social and emotional development at age 5 (primary outcome) when compared to services as usualEstablish if IY-T is effective in improving children’s early years school skills at age 5 (secondary outcome) when compared to services as usualEstablish whether the impact of IY-T on the above outcomes is moderated by (a) child age at time of intervention, (b) programme delivery mode (online versus face to face), and (c) socioeconomic statusEstimate the cost of the intervention (including delivery and training to deliver IY-T) and combine them with the effectiveness evidence through a cost-consequence analysis.

## Methods

### Registration

We have used the STROBE (2021) guidelines for reporting methods in this protocol and will use the guidelines for the publication of our results. This study has been registered retrospectively on ISRCTN, a clinical database for RCTs and effectiveness studies (ISRCTN49991769).

### Design

This effectiveness evaluation will use a quasi-experimental design. A quasi-experimental design lacks random assignment and uses self-selection (by which participants choose treatment or a lack of treatment for themselves) [26]. The analyses will use propensity score matching, where multiple control cases will be matched to intervention cases (see statistical methods for further details).

### Setting

This study is set in Bradford; a city in Northern England with high levels of socioeconomic deprivation and ethnic diversity [29]. IY-T is being delivered by Barnardo’s as part of the Better Start Bradford initiative (https://www.barnardos.org.uk/what-we-do/services/incredible-years-happy; https://www.betterstartbradford.org.uk/). Better Start Bradford is an initiative funded by the National Lottery Community Fund (previously the Big Lottery fund), which provide services for expectant families and families with children aged 0–3 in Bowling and Barkerend, Bradford Moor and Little Horton (three areas within Bradford).

Born in Bradford’s Better Start (BiBBS) is an interventional birth cohort study, which runs in parallel to Better Start Bradford, and is designed to evaluate the effectiveness of Better Start Bradford’s early life interventions [27]. BiBBS recruits pregnant women and their babies who live in the Better Start Bradford areas, regardless of intervention participation. Women complete an in-depth baseline questionnaire during pregnancy, and consent to routine linkage to their and their child’s health and education records and Better Start Bradford intervention participation. BiBBS recruits 54% of the eligible population and is generally representative of the local pregnant population, therefore the intervention and control participants in this study are also representative of this area [28].

### Ethical and safety considerations

The informed consent procedure in BiBBS includes women providing written informed consent to the evaluation of Better Start Bradford interventions using quasi-experimental methods for themselves and their child, including the use of cohort participants to create intervention and control groups, and use of routine data to evaluate interventions.

The protocol for BiBBS recruitment and collection of routine outcome data was approved by Bradford Leeds NHS Research Ethics Committee (15/YH/0455). Research governance approval was gained from Bradford Teaching Hospitals NHS Foundation Trust (BTHFT). The sponsor is the BTHFT Research Management and Support Office who are authorised to conduct independent auditing of sponsored studies. The existing ethics includes approval for the evaluation of Better Start Bradford interventions using quasi-experimental methods, including the use of cohort participants to create control groups.

IY-T is delivered as a part of usual practice. Ethical considerations with regards to the delivery of the programme can be found in the IY-T service design plan, and issues arising are managed by the service delivery team and Better Start Bradford as service commissioners, in accordance with local guidance, e.g., such as safeguarding procedures, access to appropriate mental health support. Key members of the research team are trained in good clinical practice. There are unlikely to be harms to individuals from taking part in the evaluation as it is non-invasive, and the practitioners delivering the intervention are trained in safeguarding.

### Participants

#### Eligibility criteria

To be eligible for this evaluation, participants must be enrolled in the BiBBS cohort. Whilst not all IY-T attendees will be BiBBS participants, all observations in the study sample, i.e., analysed intervention and matched comparison group, will be BiBBS participants.

Eligibility criteria for the intervention group are:

Consented to participate in BiBBSParent consented to a referral and enrolled in IY-T

Eligibility for the matched comparison group are:

Consented to participate in BiBBSParent of a child aged between 12 and 36 months at any time in the duration of service delivery (to ensure that matched cases are comparable)Parent has not been referred or enrolled in IY-T at any timepointParent has been matched to an individual in the intervention group (see statistical methods section)

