#### Intervention

IY-T is the intervention. Parents living in the BSB area with a child aged 1–3 are eligible to enrol in IY-T. IY-T receive most of their enrolled participants through their own engagement with the community directly, and also through engaging with schools and nurseries. IY-T aim to recruit approximately 12 parents to each group that they run.

Within IY-T, parents learn how to help their toddlers feel loved and secure, encourage social and emotional development, and establish strategies for developing routines, handling separation, and managing misbehaviour [15]. Parents/carers receive 3 promotional contacts prior to the beginning of the group via assertive outreach, consisting of telephone contact and at least one home visit. The initial telephone contact introduces the parents to the project and Group Facilitators, and aims to build the participants confidence in attending. The home visits are intended to create a sense of rapport between the family and Group Facilitators and alleviate any barriers that families might have in accessing the group such as crèche, language difficulties, or concerns about what the group might involve. The intervention will be delivered in a combination of face-to-face and virtual formats (dependent on lockdown rules in place during the COVID-19 pandemic at the time of the study and participant needs) by trained Group Facilitators who receive regular supervision from an accredited IY mentor.

The 13 IY Toddler Basic sessions cover eight topics:

Part one –Child-Directed Play Promotes Positive RelationshipsPart two–Promoting Toddler’s Language with Child-Directed CoachingPart three–Social and Emotion CoachingPart four–The Art of Praise and EncouragementPart five–Spontaneous Incentives for ToddlersPart six–Handling Separations and ReunionsPart seven–Positive Discipline-Effective Limit SettingPart eight–Positive Discipline-Handling Misbehaviour

Further detail on the content and delivery of the IY-T intervention, and materials, can be found here: https://incredibleyears.com/programs/. The IY-T theory of change and logic model developed by Barnardo’s for Bradford delivery states that IY-T will result in improvements in child social and emotional development over the medium and long term. The logic model is provided in a S2 File.

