**Matching variables for propensity score**		
Prenatal attachment (Prenatal Attachment Inventory)	Continuous	[10, 11, 41]
Prenatal Depression (PHQ-9)	Continuous	[10, 11, 41, 42]
Prenatal Anxiety (GAD-7)	Continuous	As above
Ethnicity	Categorical	[10, 11, 30, 41, 43]
Socioeconomic position (financial security)	Continuous	[30, 42, 44–46]
Speaks English	Binary	[30, 46]
Immigration status (proportion of life spent in UK)	Continuous	[30, 47, 48]
Length of time in COVID lockdown	Continuous	[49]

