### Data timeline

This study will use all available data since IY-T began (1^st^ September 2018) up until the end of their service delivery period (expected to be 30^th^ April 2024). Fig 1 provides the participant pathway through BiBBS cohort recruitment, participation in IY-T (or non-participation), and school entry with the outcome collected during reception year. Parents may enrol in the intervention when their child is aged anywhere between 1 and 3 years old, which means outcome data may be collected anywhere between two and four years after intervention participation. The routine education outcome in the EYFSP, which is reported by teachers at the end of children’s reception year in primary school (when child is aged 5 years old, equivalent to 60 months). The final analyses will be after August 2028, when the youngest children within the delivery period reach age 5 years.

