### Variables

The Directed Acyclic Graph (DAG) in Fig 2 identifies the confounding variables that will be used as matching variables in the propensity score [38, 39]. We will match on the 7 characteristics on the left-hand side of the graph (prenatal attachment, prenatal depression, prenatal anxiety, ethnicity, socioeconomic status, language status, and immigration status) to estimate the effect of treatment (IY-T) on the primary outcome (child social and emotional development).

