**Fig 2 pone.0291557.g002:**
[figure not shown]
Directed Acyclic Graph of associations between confounders, covariates, moderators, treatment exposure, and outcome. Notes: 1. SES = socioeconomic status. 2. The secondary outcome (children’s early years school skills) is not depicted here.

The justification for the selection of these variables is given in Table 2 below. Variables which affect program participation but not the outcomes should not be used in propensity score matching, as this increases the error in the estimated values [40]. Matching variables were therefore selected if they were thought to have an association with both uptake of treatment, and with the outcomes (child early years development), and there was evidence to suggest this was the case. See Table 2 for a summary of the evidence for using a matching variable, and the tested moderators of the effect. We have proposed that we will test the effects of four moderators: child age, programme delivery mode, family socioeconomic status, and ethnicity, however, this will only be possible if a sufficient sample size is reached.

All variables are obtained from the BiBBS baseline questionnaire, which takes place before the child is born (see https://borninbradford.github.io/datadict/bibbs/ for details).

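### The comparison-group rule applies the age half of the IY-T access condition but not the residence half, so it does not by itself ensure that controls could have enrolled

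*Protocol article*

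**What the plan says.** Under Eligibility criteria, the protocol article sets four conditions for the comparison group: consent to BiBBS, an age condition on the child, no referral to or enrolment in IY-T at any time, and a match to an intervention case. The age condition is a "child aged between 12 and 36 months at any time in the duration of service delivery (to ensure that matched cases are comparable"). No condition concerns where the family lives.

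Under Intervention, access to the programme has two parts, age and residence: "Parents living in the BSB area with a child aged 1–3 are eligible to enrol in IY-T".

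Under Setting, residence is tied to cohort entry: "BiBBS recruits pregnant women and their babies who live in the Better Start Bradford areas, regardless of intervention participation". The programme area consists of three areas within Bradford.

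On matching, the Variables section says "We will match on the 7 characteristics on the left-hand side of the graph": prenatal attachment, depression and anxiety, ethnicity, socioeconomic status, language status and immigration status. Table 2 adds an eighth, "Length of time in COVID lockdown". The text after Fig 2 states: "All variables are obtained from the BiBBS baseline questionnaire, which takes place before the child is born".

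**The concern.** The age rule carries an explicit justification, that it makes matched cases comparable. It reproduces only one of the two conditions that decide whether a parent could join IY-T. Residence is known at recruitment in pregnancy, at least a year before the child reaches 12 months, and families can move in between. A move elsewhere in the city is enough to end access, because the programme covers only three areas.

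The result is a one-sided entry route. Families who left before the window opened and did not return can be controls and cannot be cases. Families who left early in the window without enrolling are in nearly the same position, with only a short time in which to join. If such families differ in outcome from otherwise similar families who stayed, part of the estimated effect reflects who moved. They may also have had different usual services, since Better Start Bradford services are for families in the three areas and the Pilot data section reports that 85% of BiBBS families had used at least one. Balance checks on the listed matching variables would not show the problem.

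**Working it through.** **Step 1. Set the two access rules side by side.**

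| Condition | To enrol in IY-T (Intervention section) | To be a control (Eligibility criteria) |
|---|---|---|
| Child's age | 1-3 years | 12-36 months at any time during delivery |
| Living in the area at that age | Required | Not stated |
| In BiBBS, so resident at recruitment in pregnancy | Required for the analysed sample | Required |

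The only difference that bears on access is residence when the child is 1-3.

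**Step 2. Ask whether matching covers it.** The seven listed characteristics are prenatal. Lockdown length partly tracks calendar time, not address. None records a move after birth. Financial security, ethnicity, English and proportion of life in the UK may be related to moving, so matching may absorb part of a mover-stayer difference, but only indirectly.

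**Step 3. Illustrate the possible size.** The document gives no mobility figure and no outcome difference, so both inputs are assumptions:
- m, the share of matched controls who are such movers: 10-30%.
- k, the factor by which their odds of a higher score differ from stayers after matching: 1.2-1.5.

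To a first approximation, the shift in the control log-odds is m × ln(k).
- Low end: 0.1 × ln 1.2 = 0.018, and exp(0.018) = 1.02.
- High end: 0.3 × ln 1.5 = 0.122, and exp(0.122) = 1.13.

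| True OR | Movers do better | Movers do worse |
|---|---|---|
| 1.0 | 0.98 to 0.89 | 1.02 to 1.13 |
| 1.5 (the protocol's target) | 1.47 to 1.33 | 1.53 to 1.69 |

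**Step 4. Cost in power of removing such controls.** The stated requirement for the primary outcome is 334 intervention and 1002 control participants, for an OR of 1.5 with 80% power. With the proportional-odds formula, a 1:3 ratio and two-sided alpha 0.05 (assumed; not stated), N = 763.9 / (1 − S), where S is the sum of cubed category proportions. The category proportions are not given, so 1336 can be neither confirmed nor called wrong. It implies S = 1 − 763.9/1336 = 0.428, which is plausible (about 75% of children in one category). Taking that S:

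power = Φ( ln 1.5 / √[3(n₁ + n₀) / (n₁n₀(1 − S))] − 1.96 ), with n₁ = 334.

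| Controls lost without replacement | n₀ | Power |
|---|---|---|
| 0% | 1002 | 80.0% |
| 10% | 902 | 78.9% |
| 20% | 802 | 77.6% |
| 30% | 701 | 75.9% |

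**The case against.** Several stronger readings are tempting, and the document does not support them.

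- **That the controls are not comparable.** The text shows only that the age rule does not ensure comparability. The propensity score still balances the prenatal factors, and only a mover-stayer difference that remains after matching would bias the result. Every figure in Step 3 rests on assumption, and its low end is negligible.
- **That movers are found in one arm only.** Enrolled families may also move in the two to four years between IY-T and the outcome, and nothing excludes them. Children at schools outside the area can be in both arms. The one-sided group is the smaller one that left before, or early in, the 12-36 month window.
- **That controls with no chance of treatment invalidate the propensity model.** The design matches controls to treated cases, and the Included participants section speaks of the effect on the treated. That effect needs a comparable control for each treated family. It does not need every control to have had a chance of enrolling. Such controls matter only if their outcomes differ.
- **That many controls had too short a window.** Assume births spread evenly from 1 April 2016 (the earliest due date in the interim cohort profile) to 30 April 2023 (12 months before delivery ends). Then 83 of 2586 birth dates, or 3.2%, give less than 12 weeks of overlap with delivery, all at its end. Completing the programme is also not the entry criterion, because the intention-to-treat analysis counts all who enrolled after a home visit.

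Two further objections are fair. The detailed analysis plan is to be preregistered separately and could restrict the control pool or add a sensitivity analysis. And the Data management section mentions address updates only as a process that requires identifiable data; it does not show that dated address histories are complete. Neither removes the point, because eligibility is fixed in this article with its own comparability claim, but the second limits how firm the remedy can be.

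**Conclusion.** The concern holds in limited form. The comparison rule applies the age condition for IY-T and omits the residence condition, so families who had left the area before they could join may serve as controls but not as cases. Prenatal matching plus lockdown length does not directly account for this. The direction of any bias is unknown, so it could hide an effect or create one. Under the assumed ranges in Step 3 it runs from trivial to a reading of 1.33 or 1.69 for a true odds ratio of 1.5. The sample size calculation is not called into question. The change is worth making because the gap is in a stated rule and can be closed at low cost well before the final analysis, planned for after August 2028.

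**What to change.** Add one condition to the comparison-group criteria: the family lived in the Better Start Bradford area at some point while the child was aged 12-36 months during service delivery. Keep the existing exclusion of anyone referred or enrolled at any time. The BiBBS data managers would derive a yes/no residence flag before the data are anonymised, and the number of potential controls removed would be reported. This excludes the clear cases; families who left early in the window remain.

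If address data prove incomplete, keep the primary analysis as planned and add a sensitivity analysis limited to controls with confirmed residence.

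The cost is one sentence of eligibility, a check of address completeness, and a somewhat smaller control pool with the loss of power shown in Step 4. That loss is an upper figure for each share removed, because it assumes that no removed control is replaced.
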